### Implementation {16c}

A biostatistician carried out the allocation sequence before the start of the present randomized study. The doctoral student contacts potentially eligible women to recruit them, ensures that they meet the inclusion criteria, conducts an SCID interview, and makes an appointment for the first attachment representation interview. The graduate students of psychology conduct the first WMCI- interview, they then look at the allocation sequence to find out the group the participant is assigned. Two graduate students work on the project simultaneously and have received training to follow the study protocol.

## Assignment of interventions: blinding

### Who will be blinded {17a}

Blinding of the coders of the representation interviews and the mother-infant interaction is important for avoiding bias. However, two coders who rate the attachment representation interviews are not completely blinded, because one of them is a member of the intervention team. To avoid bias, the coder who rates the second representation interview does not know the group to which the participant belongs. However, the participants may talk about the intervention visits during their post-intervention interview, thus revealing their group allocation.

Similarly, the coders of the mother-infant interaction situations are not completely blinded. Oner is the main coder, doing 100% of the codings, and is not completely blinded to the sample because she has interviewed some participants and may thus know their study group status. However, the reliability coder, who does 25% of the codings overlapping those done by the main coder, is completely blinded for the group status.

The participants know to which group they belong, which is also a potential source of bias. However, in the informed consent form, they are not exactly told about the primary outcomes of the study.

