##### Mother-infant interaction

The quality of the mother-infant interaction is assessed using the Parent-Child Early Relational Assessment (PCERA) [88, 89], a video-observation method. The interaction situations are recorded by the graduate students in psychology 4–5 months postpartum. In the current study, the mother-infant interaction is video-recorded during a free-play session using a standardized set of toys. The videos are recorded in a laboratory setting to standardize the environment. The situations are analyzed according to the PCERA manual [89], which consists of 65 independent items: 29 parental, 28 children, and eight dyadic items. Ratings are based on a 5-min interactions sequence. The items are scored from 1 to 5; scores 1 and 2 represent an area of concern, 3 denotes an area of some concern, and 4 and 5 signify an area of strength. Two trained coders who have achieved an appropriate level of reliability, with more than 80% agreement with a trainer of the method, analyze the quality of the interaction according to the manual. The method has good factorial validity and evidence for convergent and discriminant validity as well [88, 90].

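### Mother-infant interaction (PCERA, secondary outcome): the coder who rates every recording may know some allocations, while the fully blinded coder is used only for a 25% reliability check

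*Protocol article*

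**What the plan says.** The section Who will be blinded {17a} opens by stating that blinding the coders matters for avoiding bias. For mother-infant interaction it then describes two coders. The main coder does all of the coding and "is not completely blinded to the sample because she has interviewed some participants and may thus know their study group status". By contrast, "the reliability coder, who does 25% of the codings overlapping those done by the main coder, is completely blinded for the group status".

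The section Mother-infant interaction gives both coders the same qualification: "Two trained coders who have achieved an appropriate level of reliability, with more than 80% agreement with a trainer of the method".

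Implementation {16c} explains how an interviewer comes to know the group. The graduate students carry out the first representation interview and "they then look at the allocation sequence to find out the group the participant is assigned". Concealment mechanism {16b} adds that the interviewer then tells the woman.

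Outcomes {12} lists mother-infant interaction as a secondary outcome. Statistical methods {20a} does not say which coder's PCERA ratings are analysed.

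**The concern.** Women know their own group, and EPDS, MAAS and MPAS are self-reports. A rating of recorded free play is one of the few outcomes here that can be made independently of what the mother expects from the intervention. That value depends on the rater not knowing the group.

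The plan has a fully blinded, equally trained coder but uses her only to measure agreement. An agreement figure describes how similar two sets of ratings are. It does not take bias out of the recordings that the blinded coder never sees, nor out of the overlap recordings if the main coder's score is still the one analysed. If the main coder tends to score women she knows to be in the intervention group more favourably, the group difference in PCERA moves by that amount, and a larger sample does not correct it.

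**Working it through.** The plan states no figure for this point, so there is none to reproduce. The check sets the coding assignments side by side, counts recordings, and then shows what assumed amounts of bias would do.

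**Who rates what ({17a}; Mother-infant interaction)**

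| | Main coder | Reliability coder |
|---|---|---|
| Share of recordings | 100% | 25%, overlapping |
| Knowledge of group | possible for women she interviewed | none |
| Training standard | over 80% agreement with trainer | same |

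Only the main coder has a rating for every recording. That her ratings are analysed is the natural reading, but it is an inference.

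**Count of recordings**

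The Abstract gives 100 women; Sample size {14} gives 60 per group, so 120.

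- Also rated by the blinded coder: 0.25 × 100 = 25, or 0.25 × 120 = 30.
- Rated only by the main coder: 0.75 × 100 = 75, or 0.75 × 120 = 90.

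The 75 or 90 is an upper bound on the problem, because she knows the group only for some women and the article does not say how many.

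**Illustration of size (assumed inputs)**

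Let f be the share of analysed ratings made with knowledge of group, and b the shift in favour of the intervention in those ratings, in SD units. Neither is in the document.

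- Shift in the group difference: d = f × b.
- Standard error with 50 per group: √(2/50) = 0.20 SD.
- False-positive rate, two-sided 5% z-test: Φ(−1.96 − d/0.20) + 1 − Φ(1.96 − d/0.20).

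| f | b | d | False-positive rate |
|---|---|---|---|
| 0.25 | 0.1 | 0.025 | 5.2% |
| 0.25 | 0.2 | 0.05 | 5.7% |
| 0.5 | 0.2 | 0.10 | 7.9% |
| 0.5 | 0.3 | 0.15 | 11.7% |
| 1.0 | 0.3 | 0.30 | 32% |

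The last row assumes that she knows every allocation, which the text does not say; it only marks the end of the range.

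**What redirecting the 25% achieves**

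If the main coder knows the group for at most 25% of recordings, giving those to the blinded coder and analysing her rating brings f to 0. If she knows it for 50%, f falls to 0.50 − 0.25 = 0.25; at b = 0.2 the false-positive rate falls from 7.9% to 5.7%.

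**Can the 25% overlap stand alone as a blinded analysis?**

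It gives 12.5 to 15 women per group. The difference detectable with 80% power is (1.96 + 0.8416) × √(2/n), which is 1.12 SD for n = 12.5 and 1.02 SD for n = 15. With 50 per group it is 0.56 SD. So the overlap cannot replace a full analysis, and the blinded ratings have to be used within it.

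**The case against.** **Disclosure and rank.** The authors state the limitation openly, the outcome is secondary, and EPDS, on which the sample size rests, is self-reported and not touched by coder knowledge. All of this stands and limits the importance. It does not make the present use of the blinded coder a good one.

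**Inference and magnitude.** The article does not say whose ratings are analysed or how many allocations the main coder knows. Both points stand. The figures above are a scale, not an estimate.

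**Mixing two coders in one variable.** This could add coder differences. But the first interview comes before randomisation (Trial design {8}), so whether the main coder interviewed a woman at that point should be essentially unrelated to arm. Coder differences then add noise rather than bias to the group contrast, and a covariate for coder absorbs the mean difference.

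**The tempting stronger reading.** Two coders rate the representation interviews (WMCI, among the primary outcomes), and "one of them is a member of the intervention team". A reader might infer that a primary outcome is rated with knowledge of group and that reassigning coders would cure it. The document does not support this:

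- {17a} states that whoever rates the second, post-intervention interview does not know the woman's group.
- The first interview precedes randomisation, so its content cannot reveal the group. A problem there would depend on who codes it and when, which the article does not state and could leave to the full protocol.
- The leak that the authors name is that "the participants may talk about the intervention visits during their post-intervention interview, thus revealing their group allocation". It reaches any coder, so reassignment would not close it.
- Restricting or cutting what women say would not be a safe remedy. WMCI rates the narrative itself, and only intervention women have these visits to describe, so ratable material would be lost mainly from one arm.

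**Conclusion.** The point holds for PCERA only. The coder who rates all recordings may know the group of women she interviewed, and a fully blinded coder with the same training is available but is confined to a 25% overlap. Part of the likely analysis ratings is therefore avoidably unblinded.

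The size of the bias cannot be computed from the document. Under assumed shares of 0.25 to 1.0 and shifts of 0.1 to 0.3 SD, the false-positive rate would run from 5.2% to 32%, and the low end is as compatible with the text as the middle. The conclusion rests on the inference that the main coder's ratings are analysed, and on the statement that the reliability coder is completely blinded. It is a worthwhile improvement to a secondary outcome. It is not an error in the primary analysis and does not extend to the WMCI coding.

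**What to change.** 1. State in {17a} and in the statistical methods whose PCERA rating is analysed for each recording.
2. Direct the blinded coder's existing 25% first to recordings of women the main coder interviewed, in both arms and chosen without regard to arm. For these, use the blinded rating in the analysis, with coder as a covariate.
3. If more than 25% of recordings are affected, have the blinded coder supply the analysis rating for as many as her capacity allows. Leave the remainder out of the blind-only analysis in step 4.
4. Report a sensitivity analysis restricted to ratings made without knowledge of group: the blinded coder's ratings, plus the main coder's ratings of women whose group she does not know.
5. Report how many recordings the main coder rated while she may have known the group, by arm.

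**Cost.** Steps 1, 2, 4 and 5 redistribute and document work already planned; step 3 needs extra coding time, and the blinded coder's capacity is not stated. The reliability sample is no longer random, so agreement must be reported as applying to that subset. The change is still practicable: the interactions are video-recorded, and 66 participants had been recruited by December 7, 2021, with recruitment still open. No change to the WMCI interviews or their coding is proposed.

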### Procedure for unblinding if needed {17b}

This is not applicable. See the “Who will be blinded {17a}” section.

## Data collection and management

### Plans for assessment and collection of outcomes {18a}

The study’s outcomes are assessed and collected using a mixed-methods approach that comprises self-reported and observation-based measurements. The data on the self-reported measurements are collected using electronic questionnaires. The data on the observation-based assessments are collected from video-recorded interviews and interaction situations. Because of the COVID-19-pandemic, the interviews may be carried out with remote connections.

The data from the questionnaires are collected and managed using the Research Electronic Data Capture (REDCap) tools hosted in the University of Turku [69, 70]. REDCap is a secure, web-based software platform designed to support data capture for research studies, providing (1) an intuitive interface for validated data capture, (2) audit trails for tracking data manipulation and export procedures, (3) automated export procedures for seamless data downloads to common statistical packages, and (4) procedures for data integration and interoperability with external sources.

#### Data collection measures

The women’s background variables’ such as parity, age, antidepressant medication, and care contacts within healthcare are collected electronically by REDCap in connection with other questionnaires before the first attachment representation interview.

#### Prenatal and postnatal depressive symptoms

Prenatal and postnatal depressive symptoms are assessed using the Edinburgh Pre-/Postnatal Depression Scale (EPDS). The EPDS is a reliable, validated, and internationally accepted 10-item self-rating instrument for screening depressive symptoms, with the score ranging from 0 to 30 points [7, 71]. For minor depression, the lowest cut-off score is 10 points [7, 71, 72]. The cut-off score for major depression varies from 13 points [73, 74] to 15 points [74]. In the Finnish cohort, the cut-off score of ≥ 12 points is used for probable depression [75]. The higher the score, the higher the probability of clinical depression.

The EPDS questionnaire is filled out electronically by REDCap at three time points: in connection with the two attachment representation interviews and the interaction observation visit in the postpartum period. During the recruitment phase, the first EPDS questionnaire is filled out voluntarily on the project’s web page by those women who are interested in participating. After their recruitment, the participants individually receive the links to the electronic questionnaires.

#### Depression

Depressive symptoms are also evaluated by The Structured Clinical Interview for Diagnostic and Statistical Manual of Mental Disorders (SCID). It is a valid, diagnostic, and widely used semi-structured interview designed to evaluate psychopathology categorically. For example, it can be used to assess the severity of dimensions of depression [76]. The interview is reliable in clinical screening as well as for research purposes and can be conducted over the phone [77]. Only the depression module of the SCID is used in the present study. The SCID is chosen to verify clinical depression and its severity.

Using the SCID, the doctoral student conducts phone interviews with eligible women upon recruitment.

#### Pregnancy-Related Anxiety

Pregnancy-specific anxiety is assessed with the Pregnancy-Related Anxiety Questionnaire Revised (PRAQ -R2) [78, 79], which is a validated and shortened version of the 34-item PRAQ [80]. PRAQ-R2 is suitable for use in pregnant women regardless of parity. It is a 10-item self-report scale that consists of three subscales: (1) fear of giving birth, (2) fear of bearing children with physical or mental handicapped, and (3) concern about one’s appearance. Each item score ranges from 1 (definitely not true) to 5 (definitely true). A higher score represents a higher level of anxiety.

The PRAQ-R2 is filled out electronically by REDCap twice in connection with the representation interviews. After their recruitment, the participants individually receive the links to electronic questionnaires.

#### General anxiety

General anxiety symptoms are measured with the anxiety subscale of the Symptoms Checklist 90 (SCL-90), which is a valid and reliable 10-item self-report, with each item rated from 0 (not at all) to 4 (extremely) [81]. It can be used in both clinical and research settings [82].

The anxiety subscale of the SCL-90 questionnaire is filled out electronically by REDCap twice, in connection with the representation interviews. After their recruitment, the participants individually receive the links to the electronic questionnaires.

#### Prenatal maternal relationship with the infant

##### Prenatal attachment

Prenatal maternal emotional attachment is measured using the Maternal Antenatal Attachment Scale (MAAS), which is a validated 19-item instrument designed to evaluate prenatal attachment to the fetus using the dimensions of “quality of attachment” (10 items e.g. experiences of closeness, tenderness, pleasure in interaction, distress at fantasized loss and conceptualizing the fetus as a “little person”) and “intensity/time spent in attachment mode” (8 items, e.g., the amount of time spent thinking about, talking to, dreaming about or palpating the fetus, quality of involvement and intensity of preoccupation). One item (feeling whether the fetus is dependent on the mother for its well-being) is excluded from either dimension but is included in the global score. A high combined score indicates a strong attachment to and relationship with the fetus [18, 83, 84].

The MAAS questionnaire is filled out electronically by REDCap twice in connection with the representation interviews. After their recruitment, the participants individually receive the links to the electronic questionnaires.

##### Attachment representations

Prenatal attachment representations are assessed using the Working Model of the Child Interview (WMCI) [85]. This semi-structured interview systematically explores the parents’ thoughts, feelings, and perceptions at the moment and in the future, about their fetus and relationship with their expected baby. This study uses a prenatal version of the attachment representation interview [28]. The interviews are conducted and recorded in either a laboratory or a home setting. Because of COVID-19 restrictions, remote interviews are also allowed, which are conducted with safe online conferencing and recording software. The interviews are carried out by the graduate students in psychology, who are trained in the interview protocol.

From the recorded interviews, representation narratives are evaluated according to the WMCI coding manual [86]. First, the narrative is evaluated with six qualitative scales (Richness of Perceptions, Openness to Change, Intensity of Involvement, Coherence, Caregiving Sensitivity, and Acceptance) and two content scales (Infant Difficulty and Fear of Infant’s Safety). The quality and content scales are coded with a Likert-type scale ranging from 1 to 5 [86]. Subsequently, the narratives are categorized into balanced, disengaged, and distorted representations. Disengaged and distorted representations can also be classified as non-balanced representations.

Two trained coders who have attained an appropriate level of reliability in their training, with more than 80% agreement between the trainer and the trainee, analyze the attachment representation interviews.

The graduate students in psychology conduct the representation interviews twice at gestational weeks 25 and at 33–35.

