### Concealment mechanism {16b}

The randomization list is kept in a locked place to which only the study group has access. After the first attachment representation interview, the interviewer looks at a separate randomization list to find out the group to which the participant is assigned and reveals it to the participant. Two graduate students of psychology carry out the interviews, which are scheduled according to the gestational weeks of the participants.

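### The second WMCI, which feeds a primary outcome, is conducted by the small group of students who look up and reveal allocation, and the stated blinding safeguard covers only the coders

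*Protocol article*

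**What the plan says.** Outcomes {12} places prenatal representations before and after the intervention among the primary outcomes. Objectives {7} adds a between-group hypothesis on the change from non-balanced to balanced representations.

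Attachment representations, under {18a}, describes the WMCI as a semi-structured interview whose recorded narrative is later coded on scales such as richness and coherence and then classified. It states: "The graduate students in psychology conduct the representation interviews twice at gestational weeks 25 and at 33–35".

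Concealment mechanism {16b} says of the step that follows the first WMCI: "the interviewer looks at a separate randomization list to find out the group to which the participant is assigned and reveals it to the participant". It also says: "Two graduate students of psychology carry out the interviews, which are scheduled according to the gestational weeks of the participants". On access it says: "The randomization list is kept in a locked place to which only the study group has access". Implementation {16c} repeats the look-up step for the graduate students who do the first WMCI: "they then look at the allocation sequence to find out the group the participant is assigned".

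Who will be blinded {17a} opens with: "Blinding of the coders of the representation interviews and the mother-infant interaction is important for avoiding bias". It then covers coders and participants. The coder of the second interview is said not to know the group. The section admits that coder blinding is incomplete and that women may disclose their group in the post-intervention interview. The interviewer is not mentioned.

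**The concern.** The interviewer produces the material that the coder scores. In a semi-structured interview, follow-up questions, pace and warmth can change how rich and coherent the narrative is. If the interviewer knows the group, these can differ between arms without anyone intending it. A coder who is unaware of the group would still score a recording already shaped in that way.

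At stake is the between-group comparison of representations, one of the primary outcomes. The issue is separate from concealment of the sequence before enrolment and from what the coders know.

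**Working it through.** No arithmetic settles this point, so the check sets the sections side by side.

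1. **Is the outcome primary?** Yes, by Outcomes {12}, and the abstract names the WMCI as one of the attachment measures.
2. **Who learns the allocation?** The interviewer at the first WMCI, by {16b} and {16c}. The list is open to the study group, and no separation between the two students is stated.
3. **Who conducts the second WMCI?** Graduate students in psychology again, by Attachment representations. {16b} gives their number: "Two graduate students of psychology carry out the interviews".
4. **Is there a rule on which student sees which woman?** None is stated. The reference to gestational weeks in {16b} concerns when interviews take place, not who conducts them.
5. **Who is covered by a blinding safeguard?** Only the coders, by {17a}, and only in part, since one of the two WMCI coders belongs to the intervention team.
6. **Does the protocol accept the premise?** Yes. {17a} says that the main coder of the mother-infant interaction may know some women's groups because she interviewed them. It applies this reasoning to coding and not to interviewing.
7. **Do other safeguards reach the interviewer?** Attachment representations says that interviewers are trained in the interview protocol, and the auditing section {23} provides supervision to keep technique consistent. Both limit variation in probing. Neither withholds the allocation.
8. **Which other primary measures are exposed?** The EPDS and MAAS are completed electronically by the woman, so the interviewer does not elicit them.
9. **Is there still room to act?** The section Trial reports 66 women recruited by December 7, 2021. The abstract gives a target of 100, so 100 − 66 = 34 remained. Sample size {14} gives 60 per group, so 2 × 60 − 66 = 54 remained. Women already recruited but not yet at their second interview would add to this, and their number is not given.

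**The case against.** The strongest reply is that the article does not say who interviews whom. Rostering is operational detail that a journal article may leave to the full protocol, and the students may already swap. Recruitment began in September 2018 and was to continue after December 2021, so the individuals may also have changed. This stands as a limit. A reader might infer that the same student sees the same woman twice, but the document neither says so nor excludes it. What remains is that the role is the same, that no separation is stated, and that the blinding section, which discusses imperfect blinding at some length, does not mention the interviewer.

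A reader might extend the point to the filmed mother-infant play, because "The interaction situations are recorded by the graduate students in psychology 4–5 months postpartum". The document does not support that. The session is free play with a standard toy set in a laboratory, and no questioning by the person filming is described.

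A reader might also infer that the bias favours the intervention. Nothing in the document fixes its direction.

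Training, recording and supervision are real protections of interview technique and count in the plan's favour. They standardise conduct but do not blind anyone.

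Finally, women may mention the ultrasound visits whoever interviews them. That is correct, and it means any change reduces the problem without removing it.

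**Conclusion.** The point holds in a limited form. The post-intervention WMCI is conducted by the same small group of students who look up and reveal allocation. The only stated blinding safeguard for this outcome applies to coders, and coder blinding cannot correct what happens during the interview.

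The size and direction of any bias cannot be derived, nor can the share of women interviewed twice by the same student, because assignment of interviewers is not described. The exposure is confined to the WMCI.

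The conclusion rests on two assumptions: that a semi-structured narrative responds to probing, and that no unpublished rule already separates the two tasks. It is a cheap improvement to one primary measure and does not call the trial as a whole into question.

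**What to change.** For women whose second interview is still to come, state in Concealment mechanism {16b}, Implementation {16c} and Attachment representations that the student who conducts the first WMCI and reveals the group does not conduct that woman's second WMCI. The other student does so, without consulting her entry on the randomization list. The last condition is needed because the list is open to the study group.

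For each second interview, record who conducted it and whether that student knew or learned the group. In Who will be blinded {17a}, name the interviewer as a remaining source of bias.

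The change needs no new staff or visits, since {16c} says that two students work at the same time. Its costs are tighter scheduling, some loss of continuity between interviewer and participant, a procedural difference between earlier and later participants, and the Ethics Committee approval that {25} requires for any protocol change. Some unblinding will remain when women mention the visits.
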